### Demographic and clinical data

Comprehensive demographic and clinical date will be collected at baseline to permit examination of factors that may influence the NeCR outcomes of participants. Demographic data (age, sex, education, marital status, employment status, living conditions and Internet use) will be collected from participants while clinical data will be retrieved from the medical record to include diagnosis, clinical presentation, documented hypertension, dyslipidemia, diabetes, any treatments being received and single/multiple vessel disease.

### Data management

Participants will be given a code to ensure anonymity. According to Chinese University of Hong Kong Policy on Research, Intellectual Property and Knowledge Transfer, data will be stored in a locked computer accessible only to the principal investigator and researcher [72]. Data entry of all questionnaires will be validated by a second person.

### Data analysis

The latest version of SPSS will be used to analyze data with a 5% significance level (two-sided). Treatment evaluation will be performed based on the principle of intention to treat. A generalized estimating equations (GEE) model will be used to compare the differential between the two groups related to each of the outcomes across the time-points, with adjustment for potential confounding variables in order to obtain a more precise estimation of intervention effect. The potential confounding variables will be selected on the basis of clinical judgment and statistical incomparability at baseline. For the smoking behavior as nominal data, the Chi-square test will be used to compare the number of patients who quit smoking between the groups. In addition, the Friedman test will be used to compare the changes in percentage of smoking cessation among the groups over time [73]. Survival analysis, the analysis of time-to-event data will be conducted to describe the length of time from entering the program to an unplanned health services utilization.

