### Study sample

The study will be conducted at four cardiology units of Tongji Hospital, Wuhan, China where CHD patients are treated conservatively with percutaneous coronary intervention (PCI) or medication and discharged under stable medication regimen. Eligibility requirements of participants are: adults aged 18 years or older; hospitalized for an initial diagnosis of CHD based on angiography or exacerbation of this condition in previously diagnosed cases; anticipated discharge to home; uses a computer and/or smartphone to access the Internet at home, reads and speaks Mandarin; minimum of primary education level; and no prescribed activity or exercise restriction. Exclusion criteria are: a diagnosis of acute psychotic disease/ life-limiting condition; absolute and relative contradictions to exercise testing and training and high risk for exercise prescription according to the American Association of Cardiovascular and Pulmonary Rehabilitation (AACVPR) guideline; and, having auditory, visual, fine motor, or ambulatory disorders.

Referring to a systematic review of studies which examined the effects of tele-cardiac rehabilitation on lifestyle behaviors, health outcomes and quality of life, the effects size on promoting healthy lifestyle is 0.42 to 1.29 so that a medium effect size of 0.5 (with 80% power and .05 significance) is conservatively adopted in this study [38]. The estimated sample size is 146, which takes into consideration an expected attrition rate of 12% based on prior studies with similar post-test time points of 6–12 weeks [31, 39]. Eligible participants will be identified by research nurses from four inpatient cardiac departments of the hospital by reviewing medical records. A second confirmation will be made with the on-site physicians. Eligible participants will then be invited to participate in this study and an information sheet will be provided. After obtaining informed consent, baseline data will be collected.

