### Randomization and data collection procedure

Eligible patients will be invited to participate in this study and an information sheet will be provided. After obtaining informed consent, baseline data will be collected. Participants will be randomly assigned to either the intervention or control group by block randomization. Three different block sizes of 4, 6 and 8 will be used. The random number for group assignment will be generated by random allocation software. The group assignment will be written and placed in an opaque sealed envelope and given to participants by the research assistant after baseline data collection (T_0_). Outcome evaluation will take place at the 6-week intervention (T_1_) and upon completion of the 12-week intervention (T_2_) by trained research assistants who are blinded as to the participants’ intervention allocation (Fig. 1). Participants will not be blinded as to their group allocation. The following parameters for outcome assessment will be used to include health behavior, emotional outcomes, health-related quality of life, cardiac physiological risk parameters and unplanned health services use. Participants’ travel expenses for data collection will be reimbursed.

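### Choosing adjustment covariates partly by baseline imbalance does not serve the precision aim; the baseline value of each outcome should be a fixed covariate

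*Protocol article*

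**What the plan says.** The Data analysis section describes the model as follows: "A generalized estimating equations (GEE) model will be used to compare the differential between the two groups related to each of the outcomes across the" time points, "with adjustment for potential confounding variables in order to obtain a more precise estimation of intervention effect". It then gives the rule for choosing those variables: "The potential confounding variables will be selected on the basis of clinical judgment and statistical incomparability at baseline". No covariate is named, no test or threshold for incomparability is given, and the baseline value of the outcome is not mentioned as a covariate.

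The Demographic and clinical data section lists what is available: "Comprehensive demographic and clinical date will be collected at baseline to permit examination of factors" that may influence outcome. It names seven demographic items and seven clinical ones.

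Under Randomization and data collection procedure, outcomes are measured at T0, T1 (6 weeks) and T2 (12 weeks), and allocation is revealed after T0: "Participants will be randomly assigned to either the intervention or control group by block randomization".

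**The concern.** The stated aim and the stated rule do not fit together. Adjustment improves precision when the covariate predicts the outcome, whether or not the arms happen to differ on it. Because T0 precedes random allocation, any difference between the arms at T0 is due to chance. Screening for imbalance therefore selects variables largely without regard to how well they predict the outcome, and the model cannot be known until the baseline data have been inspected.

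The covariate most likely to help with a continuous outcome is usually its own baseline value. The article does not fix it. Under the stated rule it may enter through clinical judgment, through chance imbalance, or not at all. At stake are a model open to choice after baseline data are seen and precision that the trial could have at no extra cost.

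**Working it through.** **Inputs.** From Study sample: "a medium effect size of 0.5 (with 80% power and .05 significance) is conservatively adopted in this study", and "The estimated sample size is 146, which takes into consideration an expected attrition rate of 12" per cent. From Data analysis: two-sided 5%. Allocation is taken as 1:1, since the ratio is not stated. The baseline-to-follow-up correlation rho is not in the document; I assume 0.3, 0.5 and 0.7. The SD is set to 1 at both times.

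**1. The plan's own figure.** For an unadjusted two-sample t-test with d = 0.5, two-sided 5% and 80% power, n = 64 per arm (power 80.1%). Then 128/(1 − 0.12) = 145.5, rounded up to 146. The stated figure is reproduced exactly, and it assumes no gain from covariates. (The normal approximation gives 63 per arm and 144.)

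**2. How often chance alone triggers the rule.** If each of the 14 listed characteristics were tested at 5% and they were independent (both assumptions), at least one would appear imbalanced in 1 − 0.95^14 = 51% of perfectly randomised trials.

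**3. Power by analysis at 64 per arm.** Power ≈ Φ(d·√(n/2)/s − 1.96), with d·√(n/2) = 0.5 × √32 = 2.828 and s² the effective variance:

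- T2 only, unadjusted: s² = 1.
- Difference in change from T0: s² = 2(1 − rho). With complete data this is the T2 group-by-time contrast when T0 is a response and the arms have separate T0 means.
- Baseline as a covariate: s² = 1 − rho².

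Example at rho = 0.5: the covariate model has s = √0.75 = 0.866, so 2.828/0.866 − 1.96 = 1.31 and power is 90%. The change contrast has s = 1, so 2.828 − 1.96 = 0.87 and power is 81%.

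| rho | T2 only | Change contrast | Baseline always a covariate | Variance ratio, change to covariate = 2/(1 + rho) |
|---|---|---|---|---|
| 0.3 | 81% | 67% | 84% | 1.54 |
| 0.5 | 81% | 81% | 90% | 1.33 |
| 0.7 | 81% | 95% | 98% | 1.18 |

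The change contrast is less precise than the covariate model at every rho below 1. It is less precise than the plain T2 comparison when 2(1 − rho) > 1, that is, when rho < 0.5.

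**4. The imbalance rule, simulated.** 6,000 trials per setting, 64 per arm, with the baseline outcome adjusted for only if its baseline t-test gives p < 0.05:

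| rho | Power, rule | Power, always adjusted | SD of estimate: unadjusted / rule / always | Type I error, rule |
|---|---|---|---|---|
| 0.3 | 80% | 83% | 0.177 / 0.175 / 0.170 | 4.4% |
| 0.5 | 81% | 90% | 0.177 / 0.172 / 0.154 | 4.1% |
| 0.7 | 83% | 98% | 0.175 / 0.164 / 0.126 | 3.7% |

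The covariate entered in about 5% of trials, as chance dictates. The SD column bears directly on the stated aim: the rule captures only a small part of the precision available. (The 83% at rho 0.3 is the simulated counterpart of the 84% from the formula.)

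**The case against.** The rule names two criteria, not one. A reader might infer that covariates are picked by significance testing alone. The text does not say so: clinical judgment comes first, and through it prognostic variables, including the baseline outcome, could enter. Nor does it specify a test or a 5% screen, so step 4 models one reading only. This stands, and it limits the numbers. It does not rescue the imbalance criterion. If both conditions are required, a known predictor enters only when it happens to be imbalanced; if either suffices, variables imbalanced by chance still enter.

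The covariate list and the handling of T0 may also be set out in a fuller protocol or analysis plan that is not shown, and a GEE across the time points probably already uses T0 as a response. That is fair: the absence of a list is not in itself a fault, and it would be wrong to say that the baseline is ignored. The point rests on the selection rule that the article does state.

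Two further inferences are tempting and unsupported. One is that the rule inflates false positives; in the simulation it is slightly conservative. The other is that it leaves the trial underpowered; 146 was sized without adjustment, and the modelled rule still gives 80% or more. Finally, screening on imbalance uses baseline data only, so the model need not be chosen with outcomes in view.

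**Conclusion.** The point holds in a limited form. Selecting covariates partly by baseline imbalance is a poor rule in this randomised trial: it follows chance, makes the model data-dependent and does not deliver the precision given as its reason.

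Under the assumed p < 0.05 reading, the loss against always adjusting for the baseline outcome is about 3 to 15 percentage points of power over rho 0.3 to 0.7. It is a loss against a better analysis, not against the planned 80%.

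If T0 is a response and the group-by-time contrast is the test (probable but not stated), the loss against baseline adjustment is about 2 to 18 points, and power falls below 80% only when rho is under about 0.5. A low rho is conceivable for physical activity, since T0 is taken around an admission and follow-up comes after discharge, but the document gives no value.

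The principle is secure. The sizes depend on rho, on equal SDs, on 64 completers per arm and on the reading of the rule.

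**What to change.** In Data analysis, remove the imbalance criterion from the covariate sentence and state instead that:

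- each model for a continuous outcome includes the baseline value of that outcome as a covariate, with T1 and T2 as the responses; or, equivalently in aim, T0 stays in the longitudinal model as a response with a common mean for both arms;
- any further covariates are named in advance, chosen on clinical grounds from the characteristics already collected;
- the unadjusted estimate is shown as supportive.

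The cost is a few sentences. The outcomes are already measured at T0 and the other characteristics are already recorded, so no new data are needed. N stays at 146.

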### Process evaluation

Experiences and perceptions of participants in the NeCR will be assessed through individual in-depth interview of a sample of 15–20 intervention group participants. Sampling will occur until theoretical saturation, which is expected to be reached by selection of 20% of the intervention participants [74, 75]. To maximize the sample variation, participants who have different responses to the NeCR in terms of the changes on their scores on the primary outcomes (0-35th percentile, >35th percentile and > 70% percentile of the score) will be recruited. The subject selection will also attempt to optimize the relevant clinical and demographic characteristics such as age, gender, education and treatment received. Interviews will be conducted by a researcher with extensive experiences in qualitative interviewing and independent of outcome assessment. The interview will focus on individual NeCR experiences, perceived effectiveness, likes and dislikes and further suggestions. Thematic content analysis will be used including an iterative process reading, coding, categorizing and identifying themes [76].

Engagement with the NeCR will be assessed using the website log file for numbers of log in and data upload. Numbers of communication with the nurse for consultation and events or issues sharing among peers will be recorded.

### Potential risks management

All personal electronic data will be stored in a password-protected account to ensure confidentiality. Participants have been informed that they will incur no additional costs for care received during the intervention and it will not replace care provided by their physician. Participation in the study will be discontinued if a participant’s health status changes and no longer meets inclusion criteria and they will be referred to appropriate care services. To minimize any possible adverse event due to exercise, patients will be advised to start exercise at their metabolic equivalent level based on a six-minute walk test and increase gradually in frequency, duration, and intensity. Participants will be encouraged to access symptom management information and contact the nurse for guidance when needed. An emergency card with participant’s name, diagnosis, contact information of the family/friend and researcher will be provided in case of an adverse event due to disease deterioration or exercise.

## Discussion

This study will use a hybrid approach guided by an empowerment model to investigate the effect of eHealth CR which integrates behavior change strategies on not only exercise but also on diet, stress and smoking. The intervention content and web-design are based on international guidelines and national culturally appropriate recommendations to improve credibility, comprehensibility and implementation for this population. Individual assessment and a collaborative approach to goal setting and action planning helps participants understand the purpose of using the web- and tele-platform. This could also encourage participants’ engagement in self-care decision making with their health care professional and proactive use of the e-platform, which are resources for self-management. Considering the continuous care needs of a patient discharged to their home setting after a cardiac event, individual consultation and guidance from a nurse and encouragement from peer interaction and support will be initiated through multi-communication channels as social motivators for behavioral goal attainment. This study uses a new method of peer support in which the researcher shares participants’ progress toward goal attainment with the peer group and encourages participants to share their experiences and concerns to reinforce behavioral changes.

### Limitations of the study

There are several possible limitations to this protocol. Although participants will be recruited from a regional hospital which serves a population with diverse demographic and socio-economic characteristics, the generalizability of the study findings will still be limited since the study involves only one province in China and excludes those residents who are illiterate. Another limitation is that self-report measures are used to monitor the level of participation in the eHealth CR and the changes in behavioral, psychological and health-related status. The findings may subject to social desirability and recall bias. Also, even though an attention placebo in the form of patient education is used in this clinical trial, none of the initiatives can ensure that an equal amount of attention is paid to both groups. This may result in a threat to internal validity.

## Conclusion

This study reports the development and evaluation of a novel eHealth CR program for the Chinese CHD population. By using a hybrid approach to integrate minimal personal contact with intensive and multimodal eHealth initiatives, the eHealth CR program addresses the limited accessibility and acceptability of the conventional CR program without scarifying its merit in providing encounters with healthcare professionals. With the detailed information about the program content and implementation plan as well as the evaluation in the process and outcome perspectives, this paper provides insights to enable the model replication or application in the management of other chronic diseases.

## Data Availability

Datasets from this study will be available from the corresponding author upon reasonable request.

## Abbreviation

AACVPR: American association of cardiovascular and pulmonary rehabilitation
BMI: Body mass index
CHD: Coronary heart disease
CR: Cardiac rehabilitation
CSES: Cardiac self-efficacy scale
DASS-21: Depression anxiety stress scale 21
GEE: Generalized estimating equations
HPLP- II: Health promoting lifestyle profile II
HRQoL: Health related quality of life questionnaire
IPAQ: International physical activity questionnaire
MET: Metabolic equivalent
NeCR: Nurse-led eHealth cardiac rehabilitation
PCI: Percutaneous coronary intervention
